### Criteria for discontinuing or modifying allocated interventions {11b}

If the participant has IDA at *T*_6w_ or *T*_12w_ defined as Hb < 11 g/dL and *s-*ferritin < 30 μg/L, an additional dose of IV iron isomaltoside is allowed in both groups (not at *T*_18w_ due to lack of AE monitoring). The maximum cumulative dose is set to 2000 mg for the individual participant.

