### Sample size {14}

The sample size calculations are based on the primary endpoint: Hb ≥ 11 g/dL (≥ 6.8 mmol/L) at all time points after baseline [1, 5]. The primary endpoint will be estimated by a Kaplan-Meier curve. Participants who drop out during the trial will be accounted for (set as ‘censored’) by the methodology and therefore not addressed specifically in the sample size calculations. It is assumed that 5% and 17.5% of the participants in the FDI and oral treatment groups respectively will have a Hb < 11 g/dL at some point during the trial, corresponding to 95% and 82.5% will have a Hb ≥ 11 g/dL at all post-baseline visits. Using a significance level of 5%, and setting the power to 80%, 100 participants in each treatment group are required in order to detect the assumed difference between FDI and oral iron.

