## Statistical methods

### Statistical methods for primary and secondary outcomes {20a}

Time to Hb < 11 g/dL and proportion of participants with correction of anaemia (Hb ≥ 11.0 g/dL) at *T*_3w_, *T*_6w_, and *T*_12w_ will be estimated by a Kaplan-Meier curve using scheduled visits. Based on the Kaplan-Meier curve, the proportion of participants who have met the primary endpoint (achievement/maintenance of Hb ≥ 11 g/dL at all post-baseline visits) at *T*_18w_ will be estimated and compared between the treatment groups.

The primary endpoint analysis will be performed for the intention-to-treat analysis set and will be repeated for the full analysis set and per protocol analysis sets.

As sensitivity, the risk difference will be used to compare the proportion of participants with Hb ≥ 11 g/dL at all post-baseline visits. Risk difference and the associated 95% Newcombe CI and *p* value will be calculated, adjusting for strata (Hb </≥ 11 g/dL at inclusion) using the Cochran-Mantel-Haenszel method. In this analysis, participants who do not complete the study period will be set as failures.

The change in Hb and biochemical safety parameters from baseline to *T*_3w_, *T*_6w_, *T*_12w_, and *T*_18w_ will be analysed using a restricted maximum likelihood-based mixed model for repeated measures approach.

The proportion of participants who (a) receive an additional IV FDI dose, (b) receive allogenic RBC transfusions, (c) discontinue from the trial because of lack of response or intolerance of investigational drugs, and (d) develop hypophosphatemia will be compared between the treatment groups by Fisher’s exact test.

The number of units of RBC transfused per transfused participant from baseline to final subject visit will be compared between the treatment groups by an analysis of variance or Wilcoxon test.

For participants in the oral iron group, AEs with onset at/after the time of first additional IV iron isomaltoside dose will be excluded from the main AE summaries. In addition, displays of all AEs per overall treatment group will be produced, as well as summaries and participant listings of AEs occurring at/after the time of first additional IV iron isomaltoside dose.

Medical record follow-up will be tabulated by descriptive statistics.

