### Methods in analysis to handle protocol non-adherence and any statistical methods to handle missing data {20c}

The intention-to-treat (ITT) analysis set will include all subjects as randomised. The per protocol (PP) analysis set will include all subjects who do not have any major protocol or GCP deviation of clinical or statistical significance. Non-compliance, i.e. treatment dose outside the 80–120% range within the first 6 weeks of treatment, is considered a major protocol deviation.

All participants in the intention-to-treat analysis set with post-baseline Hb data will be included with their observed data. Participants without post-baseline Hb values will have change from baseline set to 0 at the first post-baseline visit. The model will include the fixed, categorical effects of treatment, week, and treatment-by-week interaction as well as the continuous, fixed covariates of baseline Hb value and baseline Hb-by-week interaction. Similar analyses will be performed for the other haematological indices (reticulocytes etc.), change in fatigue, QoL, and RLS.

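### The main AE table cuts follow-up at the first additional IV dose in the oral arm only, and late oral-arm secondary means can include the effect of IV iron

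*Protocol article*

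**What the plan says.** **Additional dose.** Under Criteria for discontinuing or modifying allocated interventions {11b}, a woman with IDA (Hb below 11 g/dL and ferritin below 30 μg/L) at T6w or T12w qualifies: "an additional dose of IV iron isomaltoside is allowed in both groups". No such dose is given at T18w.

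**Adverse events.** Statistical methods {20a} states: "For participants in the oral iron group, AEs with onset at/after the time of first additional IV iron isomaltoside dose will be excluded". This concerns the main AE summaries. No equivalent rule is given for FDI women who receive a second infusion. The following sentence plans further tables, the last of them for events after that same dose: "In addition, displays of all AEs per overall treatment group will be produced, as well as summaries and participant listings of AEs occurring at/after".

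**Secondary efficacy.** Section {20c} says of the repeated-measures model for change in Hb: "All participants in the intention-to-treat analysis set with post-baseline Hb data will be included with their observed data". It continues: "Similar analyses will be performed for the other haematological indices (reticulocytes etc.), change in fatigue, QoL, and RLS". Neither {20a} nor {20c} says how a value measured after an additional IV dose is treated.

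**Primary endpoint.** This is "achievement/maintenance of Hb ≥ 11 g/dL at all post-baseline visits". The proportion of women who "receive an additional IV FDI dose" is a separate endpoint, compared by Fisher's exact test.

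Dissemination plans {31a} names AEs and change in Hb, ferritin and TSAT up to T18w as the key secondary endpoints for public posting.

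**The concern.** AEs are an incidence endpoint, collected until the final visit at about 18 weeks. If one arm's counting stops early for some women and the other arm's does not, crude percentages are no longer comparable. The main table would show fewer oral AEs because those women were observed for less time, and FDI would look relatively worse. The cut women are also not a random subset: they are the women who became anaemic.

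The same event is handled differently for the secondary efficacy endpoints. There, an oral-arm woman given IV iron at T6w contributes her T12w and T18w values to the oral mean, and one dosed at T12w contributes her T18w value. The secondary objectives compare IV FDI with oral iron, but the late oral means would describe oral iron with IV iron added where needed. A reader of the posted results would meet one convention in the AE table and another in the Hb, ferritin and TSAT tables, with nothing to explain the difference.

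**Working it through.** **Inputs from the protocol article**
- Follow-up of about 18 weeks (Study setting {9}); additional dose possible at T6w or T12w ({11b}).
- Planning rates (Sample size {14}): "It is assumed that 5% and 17.5% of the participants in the FDI and oral treatment groups respectively will have a Hb" below 11 g/dL at some point.

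**Inputs assumed, because the document gives none**
- Share of oral women given the additional dose, r: 17.5% as an illustration, 30% as a higher case, since women may enter with Hb below 11 g/dL.
- True 18-week AE incidence of 30% in both arms, with constant hazard.
- Hb gain after the additional dose: 0.5 to 1.5 g/dL.

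**Step 1: the plan's own figure.** Two proportions, 5% v 17.5%, pooled variance, two-sided 5%, power 80%, no continuity correction:

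n = [1.96 × √(2 × 0.1125 × 0.8875) + 0.8416 × √(0.05 × 0.95 + 0.175 × 0.825)]² / 0.125² = 99.1, so 100 per arm.

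This matches the stated 100 (power at 100 per arm is 80.3%). Nothing below changes it.

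**Step 2: oral follow-up removed from the main AE table** = r × (weeks left)/18.

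| r | all dosed at T6w | all dosed at T12w |
|---|---|---|
| 17.5% | 0.175 × 12/18 = 11.7% | 0.175 × 6/18 = 5.8% |
| 30% | 0.30 × 12/18 = 20.0% | 0.30 × 6/18 = 10.0% |

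The FDI arm loses 0% under the stated rule.

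**Step 3: effect on crude incidence.** With equal true incidence of 30%, the probability of an AE by week t is 1 − 0.7^(t/18): 11.2% by week 6 and 21.2% by week 12. Displayed oral incidence = (1 − r) × 30% + r × (probability by week t).

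| r | dosed at | oral incidence shown | apparent FDI/oral ratio |
|---|---|---|---|
| 17.5% | T6w | 0.825 × 30% + 0.175 × 11.2% = 26.7% | 1.12 |
| 17.5% | T12w | 0.825 × 30% + 0.175 × 21.2% = 28.5% | 1.05 |
| 30% | T6w | 0.70 × 30% + 0.30 × 11.2% = 24.4% | 1.23 |
| 30% | T12w | 0.70 × 30% + 0.30 × 21.2% = 27.3% | 1.10 |

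The true ratio is 1.00 in every row.

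**Step 4: would cutting both arms equalise follow-up?** With 5% of FDI women dosed at T6w, the FDI arm would lose 0.05 × 12/18 = 3.3%, against 11.7% in the oral arm. Follow-up would still differ.

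**Step 5: dilution of change in Hb.** With 17.5% of oral women dosed, the late oral mean rises by 0.175 × 0.5 = 0.09 to 0.175 × 1.5 = 0.26 g/dL. Net of 5% dosed in FDI, the between-arm difference shrinks by 0.125 × 0.5 = 0.06 to 0.125 × 1.5 = 0.19 g/dL.

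**Step 6: what is not affected.** The additional dose requires Hb below 11 g/dL at a scheduled visit, so a recipient has already failed the primary endpoint. The same holds for the risk-difference sensitivity analysis. T3w and T6w values precede any additional dose.

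**The case against.** The case for the plan is substantial, and much of it stands.

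- **No AE is lost.** A reader might infer that oral-arm AEs after IV iron go unreported. They do not: {20a} plans an all-AE display by overall treatment group, plus summaries and listings of the later events. What remains is that the unequal table is the one called main.
- **The cut has a rationale.** After IV iron, an oral-arm event cannot be attributed to oral iron alone, whereas a second FDI dose in the FDI arm is the same drug. That justifies an attribution table. It does not make crude percentages over unequal follow-up a fair between-arm comparison.
- **Cutting both arms has a safety cost.** It would take AEs after repeat FDI dosing out of the main FDI safety table. This stands, and with Step 4 it rules out that remedy.
- **Observed values are a legitimate choice.** The background section describes IV iron being given on oral treatment only once a woman becomes anaemic, so oral iron with later IV iron is a real strategy to compare. Treating retention of these values as an error goes too far. Moreover, the sentence on observed data concerns which women enter the model and does not mention the additional dose; the SAP, not shown, may settle the matter.
- **Visit-wise Hb of at least 11 g/dL.** A reader might infer that women who received the dose count as successes at later visits. The text does not establish this: {20a} places those proportions at T3w, T6w and T12w under a Kaplan-Meier curve, where an earlier failure could carry forward.
- **Size.** The 17.5% counts any Hb below 11 g/dL, including at T3w and T18w, does not require low ferritin, and the dose is optional. It is an illustration, not an estimate.

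**Conclusion.** The point holds in a limited form. By a stated rule, the main AE incidence table compares truncated oral follow-up with full FDI follow-up, although the additional dose is open to both arms. The under-count of oral AEs is modest: 5.8% to 11.7% of oral follow-up if 17.5% are dosed, which turns a true 30% incidence into 28.5% to 26.7%. These figures assume the share dosed, a constant hazard and crude percentages. The direction is against FDI, so the rule does not flatter the investigational product.

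The efficacy part is weaker. Late oral means for change in Hb, ferritin, TSAT, fatigue and QoL can include IV iron, which tends to pull the T12w and T18w contrasts toward no difference (0.06 to 0.19 g/dL for Hb, on assumed gains). That is a matter of labelling and one supplementary analysis. It is not evidence that the analysis is invalid, and it does not reach the primary endpoint or the sample size. No ferritin shift can be derived, because the document gives no rise after a dose.

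**What to change.** **Adverse events**
- Make the already planned all-AE display by randomised arm the lead between-arm comparison, or give it equal status with the present main summaries.
- Wherever the oral-arm cut is applied, report events per person-week beside the percentages. This corrects for the length of follow-up, though it assumes a roughly constant event rate over time.
- Do not remove AEs after repeat FDI dosing from the FDI safety table.

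**Secondary efficacy**
- Keep the all-data mixed models as the main secondary analysis and state that they are treatment-policy comparisons.
- Add one supplementary analysis of the same models, with values after an additional IV dose set to missing in both arms.

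**Cost.** SAP wording and one extra set of tables, with no new data and no change to the 100 per arm. The supplementary analysis relies on values being missing at random after the additional dose, so it should sit beside the all-data result and not replace it.

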### Interim analyses {21b}

No interim analyses are planned. The trial sponsor and the principal investigator can temporarily suspend or prematurely discontinue the trial at any time for reasons such as safety, ethical issues, severe non-compliance, and insufficient subject enrolment. The authorities will be informed promptly in case of suspension or termination, including the reason for the decision.

### Methods for additional analyses (e.g. subgroup analyses) {20b}

No additional analyses are planned.

### Methods in analysis to handle protocol non-adherence and any statistical methods to handle missing data {20c}

The intention-to-treat (ITT) analysis set will include all subjects as randomised. The per protocol (PP) analysis set will include all subjects who do not have any major protocol or GCP deviation of clinical or statistical significance. Non-compliance, i.e. treatment dose outside the 80–120% range within the first 6 weeks of treatment, is considered a major protocol deviation.

All participants in the intention-to-treat analysis set with post-baseline Hb data will be included with their observed data. Participants without post-baseline Hb values will have change from baseline set to 0 at the first post-baseline visit. The model will include the fixed, categorical effects of treatment, week, and treatment-by-week interaction as well as the continuous, fixed covariates of baseline Hb value and baseline Hb-by-week interaction. Similar analyses will be performed for the other haematological indices (reticulocytes etc.), change in fatigue, QoL, and RLS.

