### Outcomes {12}

The primary endpoint of this trial is a Hb ≥11.0 g/dL (≥ 6.8 mmol/L) at all trial visits post-baseline (*T*_3w_, *T*_6w_, *T*_12w_, and *T*_18w)._

The secondary endpoints are Hb ≥ 11.0 g/dL (≥ 6.8 mmol/L) at each follow-up visit, change in Hb and other haematological indices of ID/IDA from baseline to each follow-up visit (e.g. reticulocytes, reticulocyte haemoglobin content (CHr), *s*-ferritin, *s*-transferrin, *s*-iron, hepcidin, and calculated transferrin saturation (TSAT)), incidence of hypophosphatemia (defined as serum [*s*]*-*phosphate < 2 mg/dL) from baseline to each follow-up visit, change in fatigue and quality of life questionnaires from baseline to each follow-up visit, presence of RLS at each follow-up visit, number of participants who receive an additional IV iron isomaltoside dose at *T*_6w_ and/or *T*_12w_, reason for the additional IV iron isomaltoside dose (non-compliance, lack of effect), number of participants receiving RBC transfusions and the number of RBC units per transfused participant from baseline to final subject visit, type and incidence of AEs observed at any time until final subject visit, serious or severe hypersensitivity reaction starting at or after the first dose of randomised treatment, AEs of special interest (constipation, diarrhoea, flatulence, nausea, vomiting, abdominal pain, dyspepsia, dysgeusia, and stool discoloration), number of participants who discontinue from the trial because of lack of response or intolerance of investigational drugs, foetal bradycardia related to infusion of IV iron isomaltoside at or after GA 26, change in biochemical safety parameters from baseline to each follow-up visit, and compliance to treatment: at baseline in the IV group and at *T*_6w_ and *T*_18w_ in the oral group.

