This trial stands out from other trials regarding the rather strict policy on the gestational age time window for the five trial visits, which we consider a great strength in our study design. We thereby acknowledge that pregnancy is a state with major haemodynamic, hormonal, and physiological changes. We know that haemoglobin drops in 2nd/3rd trimester as part of a physiological process which prepares the pregnant woman for the blood loss associated with delivery [44]. Also, pregnancy symptoms such as fatigue and nausea are more common in 1st trimester and tend to subside in 2nd trimester [45, 46]. By recruiting pregnant women who are all at approximately the same GA at inclusion and thereby also at the follow-up visits, we ensure that the participants are at the same physiological stages at the respective visits. We hypothesise that this will make both the laboratory and clinical result more homogeneous between the treatment groups in that all data is equally affected by the physiological deviations during a pregnancy.

We consider the evaluation of clinically relevant outcomes as a strength in our trial, as these outcomes are very important to investigate. Optimally, we would have used a tool that has been validated in this specific population (European iron-deficient/anaemic pregnant women), which could detect differences in symptoms of ID/IDA while accounting for pregnancy. However, such a tool that fulfils all these criteria does not exist. A recent review illustrates how sparse clinical outcome reporting generally is in trials on perinatal IDA [47].

We chose two self-administered questionnaires in the official Danish versions: FACIT-fatigue and SF-12 in their unedited form (copyright protected). Permission to use the questionnaires has been obtained from the official websites. Both questionnaires are validated in a broader population. This is a limitation in our trial.

We chose the FACIT-fatigue questionnaire because fatigue is considered the most common symptom of anaemia. The questionnaire contains questions that seem appropriate for a pregnant woman and is simple, short, and manageable.

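### Entering a zero change for women with no follow-up Hb can bias the secondary change-from-baseline contrasts, mostly at 3 weeks, and misstates their precision; the effect is probably small and the primary endpoint is untouched

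*Protocol article*

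**What the plan says.** Section {20a} of the protocol article says that change in Hb and in the biochemical safety parameters "will be analysed using a restricted maximum likelihood-based mixed model for repeated measures approach". Section {20c} then separates two groups of women. For those with any follow-up value, "All participants in the intention-to-treat analysis set with post-baseline Hb data will be included with their observed data". For the rest, "Participants without post-baseline Hb values will have change from baseline set to 0 at the first post-baseline visit".

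The same section gives the model: "The model will include the fixed, categorical effects of treatment, week, and treatment-by-week interaction", with baseline Hb and its interaction with week as covariates. It ends: "Similar analyses will be performed for the other haematological indices (reticulocytes etc.), change in fatigue, QoL, and RLS".

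The outcomes concerned are secondary. Outcomes {12} lists "change in Hb and other haematological indices of ID/IDA from baseline to each follow-up visit", and Dissemination plans {31a} counts change in Hb, ferritin and TSAT at all four visits among the key secondary endpoints to be posted publicly.

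**The concern.** The rule is a single imputation of a constant, and the model cannot tell that constant from a measurement. Three things make zero a poor choice.

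- It is not the course the authors expect. The Discussion says: "We know that haemoglobin drops in 2nd/3rd trimester as part of a physiological process".
- FDI is given at the baseline visit (Intervention description {11a}). A woman infused and then lost has received the iron, yet she would be scored as unchanged. If the rule also covers ferritin, zero is least plausible there.
- It mixes two assumptions. A woman who misses only the 3-week visit is handled by the likelihood under missing at random; a woman who misses all four visits gets a fixed value.

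At stake are the treatment contrasts for the key secondary endpoints and their standard errors. The only sensitivity analysis described in {20a} concerns the primary endpoint, so no stated check would reveal the effect.

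**Working it through.** **The plan's own figure.** None is attached to this rule. The nearest is the sample size: "It is assumed that 5% and 17.5% of the participants in the FDI and oral treatment groups" will fall below the Hb threshold. With a two-sided 5% test, 80% power, pooled variance and no continuity correction, this reproduces 100 per arm (power at 100: 80.3%). It rests on the primary endpoint, so the zero rule does not enter it.

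**Inputs.** From the documents: the rule, the model, and 100 women per arm. Not given, hence assumed: the share *m* of each arm with no follow-up Hb (2–10%); the mean change *d* at 3 weeks in residual SD units; an unstructured covariance with correlations to the 3-week value of 0.7, 0.5 and 0.4 at 6, 12 and 18 weeks.

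**Bias.** Each imputed woman contributes one value, zero, at 3 weeks and nothing later. In large samples:

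- 3 weeks: bias = −(m_FDI·d_FDI − m_oral·d_oral)
- later visit *k*: b_k times that, where b_k is the regression of visit *k* on the 3-week value (here the correlation)

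Example, 5% per arm, changes +0.5 and +0.1: −(0.05×0.5 − 0.05×0.1) = −0.020 at 3 weeks; times 0.7, 0.5 and 0.4 gives −0.014, −0.010 and −0.008.

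**Precision.** For one arm, the model standard error with zeros divided by that from observed data is (1−m)·√(1 + m·d²/SD²). The table averages the residual variance over both arms. In the example the variance is 0.95 + 0.0475×(0.25+0.01)/2 = 0.956, so the standard error is √(0.956×2/100) = 0.138, against √(2/95) = 0.145: ratio 0.953.

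| Assumed change, FDI / oral (SD) | Imputed, FDI / oral | Bias 3w | 6w | 12w | 18w | SE ratio 3w |
|---|---|---|---|---|---|---|
| Hb-like, +0.5 / +0.1 | 2% / 2% | −0.008 | −0.006 | −0.004 | −0.003 | 0.981 |
| same | 5% / 5% | −0.020 | −0.014 | −0.010 | −0.008 | 0.953 |
| same | 10% / 10% | −0.040 | −0.028 | −0.020 | −0.016 | 0.906 |
| same | 2% / 8% | −0.002 | −0.001 | −0.001 | −0.001 | 0.951 |
| same | 8% / 2% | −0.038 | −0.027 | −0.019 | −0.015 | 0.954 |
| Ferritin-like, +3 / +0.3 | 2% / 2% | −0.054 | −0.038 | −0.027 | −0.022 | 1.024 |
| same | 5% / 5% | −0.135 | −0.095 | −0.068 | −0.054 | 1.052 |
| same | 10% / 10% | −0.270 | −0.189 | −0.135 | −0.108 | 1.085 |

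With equal shares the relative bias at 3 weeks is the share itself, for example 0.020/0.40 = 5% and 0.135/2.70 = 5%. The sign is not fixed. If Hb falls in both arms (−0.2 FDI, −0.5 oral) and 10% of FDI but 2% of oral women are imputed, the bias is −(0.10×(−0.2) − 0.02×(−0.5)) = +0.010, in favour of FDI.

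The one-arm ratio equals 1 at d/SD = √{[1/(1−m)² − 1]/m}: 1.44, 1.47 and 1.53 for 2%, 5% and 10%. Below that, the zeros shrink the standard error; above it, they inflate the residual variance enough to enlarge it.

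**Simulation check.** 3,000 trials of 100 per arm, maximum likelihood with a baseline covariate, 5% imputed per arm:

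- Hb-like: bias −0.020, −0.012, −0.010, −0.009; model standard error at 3 weeks 0.139 with zeros, 0.145 on observed data.
- Ferritin-like: bias −0.135, −0.095, −0.068, −0.059; model standard error 0.153 with zeros, 0.145 on observed data.
- Observed data only, over all scenarios run: bias at most 0.006 SD in absolute value, which is simulation noise.

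**The case against.** Several counter-arguments stand.

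- **Few women qualify.** The rule applies only to a woman with no Hb at any of four visits. Section {18b} provides for final-visit assessments at withdrawal and for laboratory samples at other appointments if visits are suspended; {18a} has laboratory data drawn from the hospital system. A share of 10% is closer to a stress test than a base case.
- **The benchmark is itself untestable.** Bias here is measured against missing at random. If these women truly had a mean change of zero, there would be none. The Discussion describes a fall over trimesters and gives no 3-week figure for iron-treated women. With equal loss and a larger FDI rise, the rule also pulls towards no difference.
- **The reach beyond Hb is unclear.** The rule names Hb only. The sentence on similar analyses may carry over the model without the zero. Since it also covers restless legs syndrome, recorded as present or absent, similar cannot mean identical.

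Three stronger readings are tempting, but the documents do not support them. A reader might infer that the rule always overstates precision; for ferritin-sized changes the standard error becomes too large. A reader might infer material bias at every visit; the later bias is diluted, and unequal loss can nearly cancel it (2% / 8%, Hb-like).

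A reader might also infer a large late ferritin error. One set of assumed trajectories with 10% imputed per arm moves the ferritin difference from 195 to 175 µg/L at 3 weeks and from 44 to 34 at 18 weeks (−23%). That implies a slope of 10/20 = 0.5, hence about equal SDs at both visits. If the SD fell with the difference, the slope would be 0.5×44/195 = 0.11 and the bias about 20×0.11 = 2 µg/L, or −5%. The documents give no SD or correlation to choose between these.

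**Conclusion.** The point holds in a limited form. The rule is explicit, the likelihood model does not need it, and it treats an assumed value as data. Relative to missing at random it can bias the secondary change-from-baseline contrasts, chiefly at 3 weeks, with a sign that depends on loss by arm. With equal loss and a larger FDI rise, the 3-week difference shrinks by about the imputed share. Compared with the observed-data analysis, the model standard error is about 2–9% too small for Hb-sized changes. For changes of the ferritin-like size it is about 2–9% too large with equal imputed shares, if the rule extends that far.

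These sizes rest on assumed shares of 2–10% and assumed mean changes and correlations. The actual size cannot be fixed from the article and is probably small. The primary Kaplan-Meier analysis censors dropouts, its sensitivity analysis counts non-completers as failures, and neither they nor the sample size use the rule.

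**What to change.** Remove the zero-change rule from the main mixed model and fit it to observed data only. Alternatively, use a constrained longitudinal model with baseline as a response, which keeps every randomised woman with a baseline value without inventing a follow-up value. If the zero rule is wanted, keep it as a labelled sensitivity analysis and state whether it applies to Hb alone or also to the other indices.

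The cost is a sentence in the analysis plan and a few lines of code. The small downside is that women without follow-up no longer add apparent sample size.
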